## Abstract

**Background:**

Patients with post–COVID-19 condition (PCC) experience a wide range of complaints (physical, cognitive, and mental), sometimes with high levels of disability in daily activities. Evidence of effective interdisciplinary rehabilitation treatment is lacking. A person-centered, biopsychosocial, interdisciplinary rehabilitation program, adapted to expert opinions and the patient’s needs, was therefore developed.

**Objective:**

This study aims to present a study protocol for a clinical trial to evaluate the effect of a new, person-centered, interdisciplinary rehabilitation treatment for PCC. It is aimed at improving participation in society and health-related quality of life in patients with PCC who perceive a high level of disability in daily activities or participation.

**Methods:**

A total of 20 Dutch adults, aged 18 years or older, with high levels of disability in daily activities and participation in society will be included in this replicated and randomized single-case experimental design study, from October 2023 onward. The replicated and randomized single-case experimental design consists of 3 phases. The baseline phase is the observational period, in which no specific treatment will be given. In the intervention phase, patients will receive the new outpatient treatment 3 times a week for 12 weeks, followed by a 12-week follow-up phase. During the intervention phase, the treatment will be personalized according to the patient’s physical, mental, and cognitive symptoms and goals. The treatment team can consist of a rehabilitation physician, physiotherapist, occupational therapist, speech therapist, and psychologist. The primary outcomes of the study are daily diaries, which consist of 8 questions selected from validated questionnaires (Utrecht Scale for Evaluation of Rehabilitation-Participation, EQ-5D-5L, and the Hospital Anxiety and Depression Scale). The other primary outcome measurements are participation in society (Utrecht Scale for Evaluation of Rehabilitation-Participation) and health-related quality of life (EQ-5D-5L). The secondary outcomes are physical tests and validated questionnaires aimed at physical, mental, and cognitive complaints. Effect evaluation based on daily assessments will include visual analysis, calculation of effect sizes (Nonoverlap of All Pairs), randomization tests, and multilevel analysis. In addition, other analyses will be based on ANOVA or a 2-tailed Student *t* test.

**Results:**

Data collection for this study started in October 2023 and is planned to be completed in July 2024. The results will be published in peer-reviewed journals and presented at international conferences.

**Conclusions:**

This is the first study investigating the effect of an interdisciplinary rehabilitation treatment with a person-centered, biopsychosocial approach in patients with PCC. Our findings will help to improve the treatment and support of patients with PCC.

**Trial Registration:**

German Clinical Trials Register DRKS00032636; https://drks.de/search/en/trial/DRKS00032636

**International Registered Report Identifier (IRRID):**

DERR1-10.2196/63951

## Introduction

A COVID-19 infection, caused by the SARS-CoV-2 virus, typically causes respiratory tract illness [1]. In the Netherlands, there have been more than 8.5 million COVID-19 infections since December 2019 [2]. Although most patients with COVID-19 fully recover, about 10% to 20% of them retain symptoms after recovery from the initial SARS-CoV-2 infection [1]. Post–COVID-19 condition (PCC), commonly known as long COVID, is defined as the continuation or development of new symptoms 3 months after the initial SARS-CoV-2 infection, with these otherwise unexplained symptoms lasting for at least 2 months [3]. PCC can affect anyone exposed to the SARS-CoV-2 virus, regardless of their age or the severity of the original symptoms. Although the exact number of patients with PCC is uncertain, it is believed that more than 1.7 million people across Europe may have experienced it during the first 2 years of the pandemic (2020-2021) [3]. Common symptoms of PCC include fatigue, dyspnea, anosmia, muscle aches, headache, chest pain, palpitations, cognitive dysfunction, anxiety or depression, and sleep problems [4,5].

Persistent symptoms associated with PCC seem to harm physical and cognitive function, health-related quality of life (HRQoL), and participation in society [4,6]. According to the vision of health by the World Health Organization (WHO)—as presented based on the *International Classification of Functioning, Disability and Health*—functional impairments as a result of biomedical and psychosocial factors can reduce social participation, quality of life, and the ability to perform activities [7]. Therefore, it is possible that persistent complaints of PCC can be maintained by both (defined or still undefined) biomedical and psychosocial factors. This is consistent with findings from one of our earlier prospective cohort studies, in which survivors of COVID-19 in intensive care units (ICUs) who were admitted due to severe biomedical complications in this early phase of their illness were followed over time. Patients’ levels of participation improved during the first year after ICU discharge [8]. But we also found that personal factors, such as less proactive coping, anxiety, or depression assessed 1 month after ICU discharge, appeared more predictive than biomedical (ICU-related) factors in indicating a delayed return to the patient’s habitual level of participation during the first year. These findings suggest that rehabilitation treatment for survivors of COVID-19 in ICUs should focus on strengthening personal and environmental factors to improve functioning, participation in society, and quality of life and not just on biomedical complaints. Although these findings were specifically related to survivors of COVID-19 in ICUs [8], the same treatment components may also apply to patients with an initially milder course of COVID-19 infection who go on to develop PCC. This would be in line with the advice of the WHO, which recommends that rehabilitation treatment should have a human-centered, goal-oriented, and holistic approach designed to optimize functioning in individuals with health conditions or impairments in interaction with their environment [9]. Guidelines from the WHO and others recommend an interdisciplinary rehabilitation treatment for long-lasting complaints due to PCC with a high level of disability [9-11].

Recently, multiple studies on the effect of rehabilitation treatment in PCC were published. Two systematic reviews show an uncertain-to-positive effect of physical (pulmonary) training on functional exercise capacity, dyspnea, and quality of life [12,13]. Neither systematic review found any serious adverse events for any of the physical (pulmonary) training [12,13]. In addition, 2 experimental studies found no postexertional malaise or other adverse events due to physical activity [14,15]. However, a recent study showed changes in skeletal muscle structure in patients with PCC that are associated with a lower exercise capacity [16]. Another systematic review showed that a multidisciplinary rehabilitation treatment (multiprofessional, programs were ambulatory or inpatient) may have beneficial effects on fatigue, dyspnea, physical capacity, pulmonary function, quality of life, and daily life activities [17]. However, this evidence is very uncertain due to the low level of evidence, inconsistency in the results, varying treatment programs, and varying patient characteristics. Based on the biopsychosocial focus of PCC, psychological interventions such as cognitive behavioral therapy (CBT) or acceptance and commitment therapy (ACT) could also be useful. These would be aimed at increasing psychological flexibility or strengthening a person’s resilience, depending on the patient’s problem [18,19]. In a study by Kuul et al [20], CBT was effective in reducing fatigue complaints and improving physical and social functioning in patients with PCC. Furthermore, CBT seemed to be both feasible and accepted by patients with PCC [21]. In addition, in a study of Nikrah et al [22], ACT significantly increased the resilience and HRQoL of patients with PCC. In summary, although there has been research on rehabilitation treatments for PCC, the current understanding of the most effective rehabilitation treatment approach and the effects on participation levels and HRQoL is still limited.

The precise cause of PCC remains unclear. A recent study by Appelman et al [16] showed changes in skeletal muscle structure, with severe exercise-induced myopathy and tissue infiltration of amyloid-containing deposits in the skeletal muscles of patients with PCC. Although there may be a somatic cause for PCC, a biopsychosocial approach seems promising for improving functioning in patients with PCC who perceive a high level of disability in daily activities and participation. It seems to be important to improve physical as well as mental resilience in order to optimize participation in society, despite health complaints due to PCC, by using a person-centered program focused on the various biopsychosocial factors of the patient and supported by a treatment plan from the entire interdisciplinary rehabilitation team. We therefore developed a new person-centered and tailored interdisciplinary rehabilitation treatment for patients with multiple health-related PCC complaints and high levels of disability in daily activities and participation. The treatment program is based on patients’ and health care professionals’ experiences and needs and on recommendations from the *European Physical and Rehabilitation Medicine* position paper [23]. This study aims to describe the replicated and randomized single-case experimental design (R-SCED) that is used to test the effectiveness of a 12-week, personalized, interdisciplinary rehabilitation treatment in secondary care and to evaluate changes in the recovery of participation levels and quality of life in patients with PCC.

## Methods

### Study Design

The design is R-SCED. This R-SCED study will use repeated measurements according to an AB follow-up design. In this design, patient functioning is closely monitored during a baseline phase (A), a treatment phase (B), and a follow-up phase. The length of phase A is 2 weeks. Phase B lasts for 12 weeks for all participants, and the follow-up phase lasts for 12 weeks. Figure 1 is a schematic presentation of the design, with treatment design and measurements (T0: beginning of phase A; T1: after completion of phase B; and T2: after completion of the follow-up phase). This R-SCED will be performed at Adelante Zorggroep, location MUMC+, which is an outpatient rehabilitation center in the south of the Netherlands.

**Figure 1 figure1:**
[figure not shown]
Schematic presentation of the design: (left) the R-SCED design and treatment and (right) measurements. R-SCED: replicated and randomized-single case experimental design; T0: beginning of the baseline phase (phase A); T1: after completion of the treatment phase (phase B); T2: after completion of the follow-up phase.

### Ethical Considerations

The institutional review board of Maastricht University Medical Centre, University of Maastricht, approved this study (NL83848.068.23 or METC 23-008) in July 2023. All participants provided written informed consent. All personal data will be handled in accordance with the EU General Data Protection Regulation and the Dutch Act on Implementation of the General Data Protection Regulation. (in Dutch: Uitvoeringswet AVG, UAVG). Participating patients will receive €75,00 after finishing the diaries and all the questionnaires.

### Eligibility Criteria

Adults, aged 18 years or older, having an indication for outpatient interdisciplinary rehabilitation treatment for PCC (high levels of disability in daily activities and participation based on the expert opinion of the rehabilitation physician) and with adequate Dutch literacy were eligible for inclusion. Participants will be excluded if PCC symptoms could be explained by an alternative medical disease or if they are not able to speak or read the Dutch language fluently; have no access to a smartphone, tablet, or computer; or have insufficient digital skills.

### Regular Health Care Procedure

After referral by a general practitioner or medical specialist, the rehabilitation physician will invite the participant for a first consultation. This first consultation is for validating PCC complaints and their impact on daily life activities and participation. Biopsychosocial disabling factors will be identified and possibilities for psychological flexibility will be assessed. There will also be a medical examination, and other medical diseases will be excluded. If necessary, a referral to other medical specialists in secondary care will take place. Finally, education about PCC complaints and biopsychosocial factors for the participant and partner will be given [24]. During this consultation, a decision is made on whether there is an indication for an interdisciplinary rehabilitation treatment in secondary care. If an interdisciplinary rehabilitation treatment in secondary care is indicated and the participant meets the inclusion criteria, the rehabilitation physician will include the participant for the treatment and inform them about the aim and content of the study. Potential participants will have 1 week to reflect before deciding they want to participate. If the participant is willing to participate in the study, the study treatment protocol will start.

### Baseline Phase (Phase A)

The baseline phase (phase A) is the control period of each participant. No specific treatment will be given during this period. The start of phase A is determined based on the start date of the interdisciplinary rehabilitation treatment and lasts 2 weeks. The number of days (7, 8, 9, or 10) a participant must fill in a daily diary during phase A will be randomized by a dedicated computer program (YourResearch). Phase B will start directly after phase A.

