### Treatment Phase (Phase B)

All participants will receive an outpatient interdisciplinary rehabilitation treatment in secondary care. This treatment aims to increase patients’ levels of activity, participation in daily life, and HRQoL regardless of the level of complaints they experience. During phase B, participants are invited to fill in a daily diary for 40 days (Figure 1).

The treatment team consists of a rehabilitation physician, physiotherapist, occupational therapist, speech therapist, and psychologist. The team is experienced in interdisciplinary rehabilitation treatment with a biopsychosocial approach. Education has been given and supervision team meetings are planned monthly. For each participant, the content of the interdisciplinary rehabilitation treatment will be personalized according to the participant’s individual physical, mental, and cognitive complaints and personal goals. As a result, input from the various disciplines can vary according to the participant’s problem profile and needs. The individual goals are activity- and participation-oriented and determined during the intake with the rehabilitation physician and further specified during the treatment (eg, “being able to vacuum the entire house”). The Canadian Occupational Performance Measure (COPM), administered by an occupational therapist, will be used to support individual goal setting. The COPM was developed to set treatment goals based on problems experienced by the patient in daily activities [25,26]. The rehabilitation physician is the team supervisor and has final medical responsibility for the participants during the study period.

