### Statistical Analysis

Baseline and demographic characteristics will be presented in means (SD), medians (IQR), or percentages, as appropriate.

For our primary outcome measurements, the daily dairies, the statistical analysis will be performed using the Shiny app (KU Leuven) for single-case data analysis [58]. The following steps will be taken to test the effects of the intervention. First, in visual analysis, the within-case data of the daily dairies will be plotted and visually inspected per participant with respect to within-phase (eg, level, trend, variability) and between-phase characteristics (eg, immediacy of effect, overlap, consistency) [59]. Second, the percentage of nonoverlapping pairs between phases will be used to calculate the effect size of each participant. Nonoverlapping data between phases indicate performance differences between phases and is an important part of visual analysis in single-case research [60]. The Nonoverlap of All Pairs is an index of data overlap between phases in single-case research [60]. The Nonoverlap of All Pairs equals the number of comparison pairs showing no overlap, divided by the total number of comparisons. It can be calculated as an area under the curve [60]. Third, randomization tests will be performed to test the null hypothesis; that the interdisciplinary rehabilitation treatment has no effect on participation levels and HRQoL. The observations of the baseline phase will be compared to those of the intervention and follow-up phases, respectively (*mean phase A – mean phase BC = test statistic*, where C is the follow-up phase). Because the starting point of phase B (intervention) is randomly determined and the follow-up phase does not include any new intervention methods, phase B and the follow-up phase are combined. In case visual analysis suggests delayed effects, the randomization test will be repeated with lagged data until the lowest *P* value has been reached. Fourth, in a SCED study, 1 outcome is repeatedly measured in the same person. These replicated single-case experiments may be considered as multiple studies that can be combined using meta-analytical procedures [61,62]. To evaluate the overall changes in the daily diaries the daily data in phase A, phase B, and follow-up a multilevel analysis will be used to summarize the single-case data. Previously calculated effect sizes will be combined.

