Missing data will be handled according to the randomized-marker method, in which all days of the diary that were not completed will be displayed as “N/A” (not applicable) [63].

For the other primary outcome measurements (USER-P and EQ-5D-5L) and the secondary outcome measurements, the results on T0, T1, and T2 will be computed as total scores on each questionnaire individually. Outcomes will be presented in mean (SD) or median (IQR), depending on the distribution. Outliers will be checked, defined as values more than 3 times the IQR from the median. The statistical analysis of the questionnaires will use repeated measures ANOVA in case of normal distribution or the Friedman test in case of nonnormal distribution. The statistical analysis of the physical examination will use the paired 2-tailed Student *t* test in case of normally distributed variables or the paired Wilcoxon test in case of nonnormally distributed variables. The significance level was set at *P*=.05, 95% CI. The statistical analysis will use IBM SPSS statistics version 26. No imputation will be made for missing data.

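### With four possible baseline diary lengths, a randomization test run per participant cannot give a P value below .25, and the article does not say whether the test is individual or pooled

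*Protocol article*

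**What the plan says.** All places are in the Methods of the protocol article.

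- **Baseline Phase (Phase A):** "The number of days (7, 8, 9, or 10) a participant must fill in a daily diary during phase A will be randomized". The same section, and Study Design, give phase A a length of two weeks.
- **Treatment Phase (Phase B):** "participants are invited to fill in a daily diary for 40 days".
- **Follow-Up Phase:** the number of diary days in the last two weeks is also randomized among 7, 8, 9 or 10.
- **Statistical Analysis, step 3:** "Third, randomization tests will be performed to test the null hypothesis", namely that treatment does not affect participation or HRQoL. The statistic is "mean phase A – mean phase BC = test statistic". The reason given for merging treatment and follow-up begins "Because the starting point of phase B (intervention) is randomly determined". If visual inspection suggests a delayed effect, the test is repeated on lagged data.
- **Statistical Analysis, other steps:** steps 1 and 2 (visual analysis and Nonoverlap of All Pairs) are explicitly per participant. Step 4 brings the cases together through a multilevel analysis and a combination of the effect sizes.
- **Statistical Analysis, questionnaire and physical-test paragraph:** "The significance level was set at *P*=.05, 95% CI". No other level is stated anywhere.

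**The concern.** The randomization test is the procedure named for testing the null hypothesis on the daily diaries, which are a primary outcome. Its P value is the share of possible assignments whose statistic is at least as extreme as the observed one. The observed assignment always counts, so the number of assignments sets a floor that no treatment effect can lower.

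With four baseline lengths that floor is far above any conventional level. If the test is run participant by participant, up to 20 nonsignificant results follow whatever the treatment does, and a reader of the results could take them as evidence against an effect. If a pooled test is intended, it is not stated, and the choice between individual and pooled testing would remain open after the data are seen.

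**Working it through.** **The plan's own figures.** The article states no minimum attainable P value, so there is none to reproduce. Its sample size of 20 comes from a calculation tool whose dropout rate, autocorrelation and sidedness are not given, so that figure can be neither confirmed nor refuted.

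**Inputs.** Four baseline lengths (Baseline Phase); statistic A versus BC with a random start of B (Statistical Analysis); level .05 (Statistical Analysis, questionnaire paragraph); 20 participants (Sample Size Calculation). Sidedness of the randomization test is not stated, so both versions are considered.

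**1. Floor for one participant.** Minimum P = 1 / (number of equally likely assignments) = 1/4 = .25. The attainable values without ties are .25, .50, .75 and 1.00. A two-sided test using the absolute difference keeps the floor at .25; doubling a one-sided P raises it to 2 × .25 = .50.

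**2. Assignments needed.** For an individual P of .05, 1/.05 = 20 equally likely assignments are required. The design has 4.

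**3. Does anything in the plan lower the floor?**
- *Lagged repeats.* Lagging shifts the data but adds no assignments. Full enumeration of the four start points on simulated series, with effects from 0 to 100 SD and lags 0 to 7, gave a lowest P of exactly .25.
- *Randomized follow-up length.* This does not move the boundary between A and BC. Crediting it anyway gives 4 × 4 = 16 assignments and 1/16 = .0625, still above .05.

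**4. Floor for a pooled test.** With k participants randomized independently there are 4^k joint assignments, and the floor is 4^-k:

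| k | Floor |
|---|---|
| 1 | .25 |
| 2 | .0625 |
| 3 | .0156 |
| 20 | about 9.1 × 10^-13 (4^20 = 1,099,511,627,776 assignments) |

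Pooling therefore removes the floor as an obstacle from three participants on.

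**5. A low floor is not the same as adequate power.** As context only, a simulated pooled test with 20 participants, 48 observations after baseline, one-sided .05, independent errors and 400 runs gave power of about .46 for a shift of 0.5 SD, .79 for 0.8 SD and .92 for 1.0 SD. These figures rest on an assumed model, and the SD here is the day-to-day SD within a participant, so they do not test the article's sample size.

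**6. What was randomized.** Study Design and Baseline Phase fix phase A at two weeks, work back from the treatment start date, and randomize the number of diary days. Statistical Analysis says the start of phase B is random. If the calendar start is not random, the basis for even four assignments is weaker. This does not rescue the individual test, and it also bears on a pooled one.

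**The case against.** The strongest reply is that the article never says step 3 is done per participant. Steps 1 and 2 carry that wording and step 3 does not. Its null hypothesis is about the treatment in general, and a sample size expressed as a number of patients fits inference across patients. The .05 level stands in the paragraph on questionnaires and physical tests, while the diary analysis uses different software and states no level. Group-level inference on the diaries is planned through the multilevel analysis. Details of pooling are often left to a full protocol or analysis plan, which is not shown here.

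Much of this stands. Both the per-participant reading and the use of .05 for this test are inferences. The per-participant reading is still the natural one: the test sits between two case-level steps and the step that combines cases, lagging is triggered by visual inspection done case by case, and the combination described covers a multilevel model and effect sizes but not randomization tests. The level matters little, because .25 fails any conventional threshold. Nor is this only an omission: the number of baseline lengths is a design feature, and no analysis plan can bring an individual P below .25.

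A reader might go further and infer that the trial cannot show a significant effect on the diaries, or that the plan commits itself to 20 individual tests at .05. The documents support neither. A pooled randomization test can reach .05, the multilevel analysis is separate, and USER-P and EQ-5D-5L have their own tests.

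**Conclusion.** The concern holds in a limited form. If the randomization test is run per participant, its smallest P is .25 and its power at .05 is zero for every participant, whatever the effect. The article does not say whether the test is individual or pooled, so as written it permits a test that cannot reject.

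The floor of .25 is exact, given four equally likely assignments. Applying it to this plan rests on two inferences: that step 3 is per participant, and that .05 applies to it. The pooled remedy assumes that the start of phase B was in fact randomized independently among the four options, which the two-week statement puts in doubt. The figure 4^20 also assumes that all 20 participants are analysed, although the article allows for loss to follow-up and does not replace withdrawals. The point is confined to the randomization test.

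**What to change.** Before analysis, amend Statistical Analysis to state the following:

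1. The randomization test is one pooled test per outcome. The statistic is the mean, over the k analysed participants, of the A versus BC difference. It is referred to the joint distribution of the 4^k assignments by Monte Carlo sampling, with sidedness and significance level given.
2. Individual randomization P values have a floor of .25 and are not interpreted against .05. Individual results rest on visual analysis and Nonoverlap of All Pairs.
3. The multilevel analysis is retained as separate group-level inference.

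Also reconcile Study Design and Baseline Phase (phase A lasts two weeks, the diary count is randomized) with Statistical Analysis (the start of phase B is random). State what was actually randomized, because the reference set of the pooled test must match it.

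The cost is analysis wording only, with no new data. According to Results, recruitment was completed in July 2024 and analysis follows the end of data collection. The number of baseline options can therefore no longer be changed for those enrolled, but the test can still be fixed before the results are seen.
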